### 2^nd^ phase: Experience‐based co‐design workshops

5.3

Participants who wish to participate in the follow‐up workshops, will register their interest through the consent form. We will aim to recruit a representative sample across adolescent and adult services by including young people and carers who did not yet undergo the transition process as well as young people and carers who have already moved to adult services. Similarly, mental health professionals from adolescent and adult services may share conflicting experiences about transition processes, discharge preparation, and parallel care. The first group may primarily express uncertainties and fears, related to the transition process, while the second group may report on their specific (positive and negative) experiences during transition. Young people (*n* = 4), carers (*n* = 4), mental health professionals (*n* = 4) and members of the research team (*n* = 3) as well as the Principal Investigator (PI) will participate in the four EBCD workshops. Our aim is to involve the same group of young people, carers, and mental health professionals in all four EBCD workshops to maximise consistency and transparency. However, every participant will have the option to withdraw or choose not to attend subsequent workshops if they wish to do so.The PI and supervisor of the team will attend all EBCD workshops.All workshops will last 3 h with two 15‐min breaks and one 30‐min lunch break in‐between. The EBCD methodological approach includes 20 min of filmed content that highlights, from the interviews and focus groups, current service user transition experiences. Using PPI feedback, we will review the content and duration of the video and extract quotes that capture the transition process according to the lived experience of young people and carers. Content deemed as too sensitive will be excluded. Participants will be reimbursed with £30 for each EBCD workshop. These rates are based on PPI rates according to the National Institute for Health nad Care Research (NIHR) guidelines to acknowledge lived experience contributions in the project.

#### 1^st^ workshop: Discuss and reflect on the video content

5.3.1

In the first part of the workshop (1.5 h), the participants will discuss the findings from the interviews and focus groups and how these can inform the intervention. During the second part of the workshop, the participants will watch the 20‐min video, taking notes throughout. The main themes presented will then be discussed and participants will be encouraged to brainstorm themes which they found important based on their lived experiences. The prominent ideas will be shared on a Padlet and used for the second workshop.

#### 2^nd^ workshop: Developing module themes for Transition for Eating Disorder Youth intervention

5.3.2

The participants will reflect on the themes elicited from the 1^st^ workshop and then themes will be further developed on the premise of capturing the priorities and lived experience of transitioning from the perspective of the young people and the carers. The participants will collaboratively create an experience map outlining barriers and facilitators for an optimal transition experience. The initial design of TEDYi will be shown to the participants as it was first proposed by the research and clinical team. We will discuss the format and structure of the design and ways of increasing engagement.

#### 3^rd^ workshop: Adapting materials

5.3.3

Participants will review the ECHOMANTRA documents and provide input regarding its adaptation in TEDYi. Psychoeducation materials are provided for both young people and their carers, who are also involved in their meal practice. The outcome measures of this intervention will be discussed in relation to transition preparedness, mental health symptoms (depression, anxiety, self‐harm, suicidality), physical symptoms (cardiovascular problems, electrolyte imbalances, hypoglycemia) and quality of life.

#### 4^th^ workshop: Meta‐workshop feedback

5.3.4

The first part of this workshop will focus on reviewing and refining TEDYi content based on previous feedback. We aim to receive feedback on these specific outcome scales: Hospital Anxiety and Depression Scale (HADS; Zigmond & Snaith, 1983), Depression Anxiety and Stress Scales (DASS‐21; Lovibond & Lovibond, 1995), ED Symptom Impact Scale (EDSIS; Sepulveda et al., 2008), The Caregiver Skills Scale (CASK; Hibbs et al., 2015), Transition Readiness Assessment Questionnaire (TRAQ; Wood et al., 2014). These scales were utilised in previous studies exploring transition experiences and evaluating transition interventions in CAMHS and were recommended by the wider research team as potential indicators to assess participants transition experience post‐TEDYi implementation (Singh et al., 2023). Therefore, we aim to ask participants whether they think these scales are suitable and appropriate for the specific group we are targeting in terms of age and clinical presentation. Last, we will receive feedback from the participants regarding the evaluation and EBCD process. The second part of this workshop will include a dissemination event organised at King's College London (KCL) to celebrate the outcomes of the workshops and the contributions of the participants.

### Study setting

5.4

This study will take place in four National Health Services (NHS) Trusts across England including both adolescent and adult ED specialist services. Interviews, focus groups and EBCD workshops will take place across all participating sites. Participants may instead choose to participate in the study through online interviews and focus groups on Microsoft Teams. Using multiple sites will allow further understandings and perspectives on similarities and differences in the transition process. The research assistants of the project will assist with recruitment (visiting sites to present the study objectives), virtual meetings with collaborators across the participating sites and data collection and analysis.

### Recruitment and sampling technique

5.5

Local collaborators across four NHS Trusts and ED units will facilitate recruitment by identifying eligible young people who are close to 18 years and will be moving to adult services within the next year from the starting date of the study and/or young people who have recently transitioned to adult services or are attending an outpatient community team. The same process will be applied for eligible carers. During weekly community meetings and adverts on boards, the collaborators will invite young people to participate in the study. Young people and carers attending adult outpatient services will be contacted through post/phone by their responsible clinician. Additionally, the study will be advertised by local collaborators through leaflets/posters in ED specialist services. Young people will contact their responsible clinician if they want to participate, who will then inform the research team. In some cases, young people and their carers may be initially contacted by an invitation letter signed by their care coordinator/clinician. A follow‐up phone call/email will be made by CAMHS or Adult Mental Health Services personnel if they do not respond to the original invitation. Purposive sampling will be used to identify eligible young people, and convenience sampling for carers and mental health professionals. The sample will be proportionally stratified to represent diverse demographic characteristics if more than 15 participants are identified in each group. The sample size was decided based on information power allowing for sufficient information, diverse experiences, and new knowledge, as well as previous studies conducted with qualitative design and estimated number of eligible participants after consultation with local collaborators. Accordingly, our targeted population is expected to share sufficient information about transition experiences and will provide new knowledge for analysis. See Figure 1 for recruitment and study procedures.

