## INTRODUCTION

1

Eating disorders present a significant public health concern and pose a chronic issue to child paediatric mental health services due to their high mortality and relapse prevalence (Walker & Lloyd, 2011). Eating disorders are life‐threatening diseases which can result in premature death among young adults, with the highest mortality rate among all psychiatric disorders and they are linked to poor psychosocial outcomes, mental health comorbidities and repeated hospital admissions (Berends et al., 2018; Cardi et al., 2017; Treasure et al., 2011). An estimated one‐third of all deaths in young people with anorexia are due to cardiovascular issues, and 25% of this population have attempted suicide. Anorexia (AN) and bulimia nervosa (BN) are the most prevalent types of EDs among young people, and they exhibit alarming symptoms ranging from starvation to purging and using laxatives to excessive exercising. Eating disorders typically first appear in adolescence and early adulthood (Arcelus et al., 2008) where two thirds of cases continue for 9 years and a third for over 20 years (Eddy et al., 2017).

Young people often present to Child and Adolescent Mental Health Services (CAMHS) with overlapping symptomatology of AN and BN due to the diagnosis complexity underlying EDs. A study found that the mean age for young people presenting in CAMHS is 14.6 years and only 27.7% are transitioned to adult services (Arcelus et al., 2008). However, a considerable proportion is not accepted by adult specialist services and might be seen by generic services or treated in primary care, which is worrying due to lack of staff training and skills around EDs (Winston et al., 2023). Studies show that young people with EDs are more likely to experience poor transitions due to lack of continuity of quality care and fragmented social support in the community (Bryan et al., 2022). Young people experiencing poorly managed transitions which do not promote graded and flexible pathways are less likely to take ownership of their condition and, therefore become more prone to poor mental health outcomes (NHS, 2019). A large‐scale national survey identified substantial barriers to ED transitions, including the absence of personalised transition plans and limited involvement of carers. Additionally, the survey highlighted a therapeutic disconnect between child and adult care plans, as adult services often lacked a developmental approach to treatment (Winston et al., 2023).

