## THEORETICAL FRAMEWORK

2

Transition for Eating Disorder Youth intervention will be informed by previously effective intervention transition models‐ECHOMANTRA and TRIANGLE‐ for adult patients with EDs. ECHOMANTRA is a skills‐training intervention for patients and carers aimed to sustain recovery after discharge based on the interpersonal cognitive model (Treasure & Schmidt, 2013) which proposes that improving patient and carer communication will lead to better transition outcomes (Adamson et al., 2019). ECHOMANTRA includes coping strategies, for recovered ED patients, towards reconstructing an identity that is not emanated from the ED. Previous research has found that individuals with AN are particularly vulnerable to family members' expressed emotions (overprotection and criticism), due to excessive worry and anxiety (Rienecke, 2018). Research shows that add‐on interventions such as ECHOMANTRA facilitates psychosocial functioning and improves outcomes for people with EDs and their carers (Cardi et al., 2017). Thus, the aim is to equip carers with skills that will foster positive emotional responses in young people with EDs. Furthermore, it is well‐established in the extant literature that carers are often excluded from adult care‐plans (Eisler et al., 2022), both due to confidentiality and expectations that individuals are well‐skilled to manage an independent lifestyle once they have transitioned. However, young people previously hospitalised in highly supportive settings transferred to adult care and/or community settings which follow a more independent care model, often lack life‐skills, and encounter major challenges in leading an adult‐like lifestyle (Webb & Schmidt, 2021). Research evidence suggests that carer involvement in young people's care journey has the potential to reduce loneliness, and social isolation by empowering the young person (Cardi et al., 2017). Thus, carers will be included in the co‐production plan to reflect on their lived experiences of transition and voice their needs. Mental health professionals will also be included to facilitate the transition process, specifically, the *letting go* period for the young person. Young people often build strong attachments to keyworkers in services and ending therapeutic relationships may be a triggering factor for relapsing during transitions.

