## RESEARCH QUESTIONS

4

What are the views and perspectives of young people, carers, and mental health professionals about transitioning from adolescent ED services to adult care?What are the personal reflections of young people, carers, and mental health professionals on the proposed content and structure of TEDYi?What changes do young people, carers and mental health professionals recommend to TEDYi structure, format, and delivery?How can TEDYi be improved based on personal lived experiences of young people, carers, and mental health professionals?How can carers be involved in transition preparation and planning?What factors should TEDYi entail for successful and sustainable implementation in adolescent services long‐term?What strategies can be employed to improve joint working between adolescent services and adult services and facilitate the promotion of TEDYi?What strategies can we implement to maintain engagement, participation and adherence in young people, carers, and mental health professionals?What measures can be put in place to provide optimal support to both carers and mental health professionals during the transition process?

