### Eligibility criteria for participants

5.6

The following inclusion criteria are for young people: (1) 16–21 years with a primary diagnosis of ED either BN or AN based on DSM‐5 criteria; AND (2) 16–21 years with EDs who are currently in TIER 3/4 ED specialist units; OR (4) 18–21 years with EDs who have moved from TIER ¾ (outpatient/inpatient care) ED specialist units to adult services and/or the community.

The following inclusion criteria are for carers: (1) carers of young people 16–21 years with EDs who are due to transition or have experienced transition to adult mental health services and the community.

Inclusion criteria for mental health professionals are as follows: (1) mental health professionals working in ED specialist adolescent units and/or adult units (nurses, psychologists, nutritionists, psychiatrists, family therapists, peer‐support workers, occupational therapists).

The following are the exclusion criteria for young people: (1) young people with EDs below 16 and over 21 years; OR (2) young people with a primary diagnosis of psychosis, and/or substance use disorder; OR (3) young people who find it difficult to communicate in English and cannot understand what is expected of them.

The following are the exclusion criteria for carers and mental health professionals: (1) lacking capacity to give informed consent due to severe morbidity (acute phase of mental illness), OR (2) not able to communicate in English

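### Carers left out of adult care are likely to be under-represented, because carers of young people already in adult care are reached through services and sampled by convenience

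*Protocol article*

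**What the plan says.** Section 5.5 (Recruitment and sampling technique) of the protocol article sets the route to carers on the adult side: "Young people and carers attending adult outpatient services will be contacted through post/phone by their responsible clinician". It adds identification by local collaborators, posters and leaflets in specialist eating disorder services, invitation letters signed by a clinician or care coordinator in some cases, and a follow-up contact by adolescent or adult service staff for those who do not reply. Young people are sampled purposively, but the method is "convenience sampling for carers and mental health professionals". The one diversity control is conditional: "The sample will be proportionally stratified to represent diverse demographic characteristics if more than 15 participants are identified in each group".

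Section 5.6 admits carers of young people "who are due to transition or have experienced transition to adult mental health services and the community". It does not require the carer to be involved with, or known to, the adult service.

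On the substance, section 2 states that "carers are often excluded from adult care‐plans" and gives confidentiality and expectations of independence as reasons. The introduction lists "limited involvement of carers" among the barriers to transition. Research question 5 asks: "How can carers be involved in transition preparation and planning". Question 9 asks, in part, how carers can best be supported during transition.

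**The concern.** The study wants to learn how carers can be brought into a process from which, on its own account, adult services often leave them out. For carers of young people who have already moved, the main stated way in is the adult service itself. A carer whom that service keeps at a distance is less likely to be contacted by its clinician or to visit a building where a poster hangs. The confidentiality that section 2 gives as a reason for exclusion may also restrain the clinician from writing to the carer. The chance of being recruited is then plausibly related to the experience under study.

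If so, the interviews would hold too little first-hand testimony about being shut out of adult care, and the carer content of the intervention would be shaped more by carers for whom contact had worked. The risk carries into the co-design stage. Only four carers take part in the workshops, they come from those who register interest on the consent form, and they are meant to span carers before and after transition.

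**Working it through.** No formula applies. The carer sample of 15 is justified by information power, earlier qualitative studies and an estimate of eligible participants, so there is no sample-size calculation to reproduce. The check sets the sections side by side.

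1. **Who is eligible.** Under section 5.6, a carer of a young person aged 16–21 with an eating disorder who is due to move or has moved. A carer left out of adult care qualifies.

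2. **Who is reached after transition.** Each route in section 5.5 has the same channel:
 - The responsible clinician's post or phone contact depends on the adult service.
 - Identification by local collaborators depends on the participating sites.
 - Posters and leaflets reach people who visit the services.
 - Letters are signed by a clinician or care coordinator.
 - The follow-up contact, which adolescent service staff may also make, applies only to people already invited. It cannot reach a carer who never received a first invitation.

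 No route through the young person is stated. First contact by the discharging adolescent service with carers of young people who have left it is not stated clearly either. It is not ruled out, since the sites include adolescent services (section 5.4) and the collaborators' process is extended to carers.

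3. **Whether sampling corrects this.** Convenience sampling takes whoever these routes produce. The proportional stratification is demographic and operates only above 15 identified people per group. Neither element refers to involvement in adult care. The reach of recruitment is therefore narrower than the eligibility rule, along a dimension central to question 5.

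4. **Size.** Two inputs would be needed: how many of the 15 carers are post-transition, and what share of such carers are excluded. The article gives neither; section 2 says only that exclusion is frequent. As an illustration, assume 5 to 10 post-transition carers and an exclusion share of 30% to 70%. Expected excluded carers in an unselected sample = post-transition carers × share:
 - low end: 5 × 0.30 = 1.5
 - high end: 10 × 0.70 = 7

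 These numbers show only that, under those assumptions, such carers would form a visible part of an unselected sample. How many the stated routes would miss also depends on how contactable excluded carers are, and the article is silent on that. The shortfall cannot be computed.

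**The case against.** A reader might infer that question 5 will be answered only by carers who are already involved, and that the stated route will yield almost no excluded carers. The document does not support either reading, for four reasons.

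- Section 2 speaks of exclusion from care plans, not from contact lists. A carer outside the plan may still be on record as a parent or next of kin and be reachable by letter or phone. Being contacted does not show that the carer is involved. The wording about attending outpatient services is loose and should not be read as a condition of eligibility.
- The clinician is not the only route, as the list above shows.
- Question 5 concerns preparation and planning, and the intervention is to be used 3–6 months before discharge. Carers whose young person has yet to move are direct informants on that. The 15 young people and 15 professionals can also describe how carers are treated.
- Section 3 covers moves within the last 5 years, so a carer in contact now may report exclusion at an earlier time.

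The article is also condensed, and its recruitment flow diagram is not available in the text reviewed, so operational detail may exist elsewhere.

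All of this stands, and it limits the claim. It does not remove it. Carers who have not yet met adult services, and staff, cannot give a first-hand account of being a carer kept out of adult care. The sampling method and the conditional stratification are stated choices, not details left to a fuller document. Nothing in them seeks variation in involvement.

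**Conclusion.** The concern holds in a limited form. Carers excluded by adult services are eligible but likely to be under-represented among the carers who inform question 5, the carer part of question 9 and the workshops. The article has no sampling criterion that would correct this. They need not be absent, and the other participant groups cover part of the same ground.

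The conclusion rests on one assumption that the document makes plausible but does not prove: that carers left out of adult care plans are, on average, harder to reach through the adult service than carers who are included. The direction follows from that assumption; the size is unknown. Since the remedy is cheap, it is worth making before carer recruitment closes.

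**What to change.** In section 5.5:

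- Ask each carer of a young person already in adult care one screening question: whether the carer is, or was, included in the young person's adult care.
- Replace convenience sampling for these carers with purposive sampling that includes both answers within the existing 15. A fixed quota is not needed. Where interest allows, seek the same variation among the four workshop carers.
- Allow the invitation also to be passed on by the young person, or by the participating adolescent service with the young person's agreement, with replies going directly to the research team. The agreement matters, because contacting the carer of someone who is now an adult raises the confidentiality issue that section 2 names.
- Report the carers' involvement status with the findings, and note possible under-representation if few excluded carers are reached.

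The cost is a minor amendment, one additional question and slightly slower carer recruitment. No extra participants are needed.
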